### Statistical analysis

Statistical analysis will be undertaken using both intention-to-treat (ITT) and per-protocol (PP) analyses. For the ITT analysis, all patients who undergo the Zelen-type randomization and received at least one treatment will be analyzed. Primary PP data analysis will also be undertaken for all patients who have high compliance (patient compliance rates equal to or greater than 80%) and do not use drugs or treatments prohibited by the protocol during treatment.

The statistical analysis will take the form of a non-inferiority test. The margin of non-inferiority is -2. For the main outcome, we will calculate the 95% confidence interval for the difference in NRS pain score between the treatment group and the control group. If the lower limit is greater than -2, non-inferiority will be considered valid.

For continuous data, mean ± standard deviation will be used to describe data that conforms to a normal distribution, whereas non-normally distributed continuous data will be described as the median (interquartile spacing). Where the data conforms to a normal distribution, independent sample t-test will be used for comparison between the two groups with homogeneity of variance; otherwise, a t-test will be used with heterogeneity of variance. Wilcoxon rank-sum test will be used if data does not conform to a normal distribution. Categorical data will be represented by frequency or percentage and compared using chi-square test or Fisher exact test. Missing data will be replaced according to the last observation carried forward method. The 95% confidence interval will be calculated, and *P* < 0.05 will be considered to indicate a significant difference. All statistical analysis will be performed using SPSS software (version 20.0).

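### The interval that decides non-inferiority has no stated method, and the only methods given for continuous data are chosen by pretests, with a rank-sum branch that carries no margin

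*Protocol article*

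**What the plan says.** The Statistical analysis section of the Protocol article has two layers.

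- **Rule for the main outcome.** "For the main outcome, we will calculate the 95% confidence interval for the difference in NRS pain score between the treatment group and the control" (that is, ILM against TM). The criterion is "If the lower limit is greater than -2, non-inferiority will be considered valid", and "The margin of non-inferiority is -2". No normality condition is attached, and no method for the interval is given.
- **General rule for continuous data.** The next paragraph begins "For continuous data, mean ± standard deviation will be used to describe data that conforms to a normal distribution" and gives median and interquartile range otherwise. For comparisons, "independent sample t-test will be used for comparison between the two groups with homogeneity of variance"; with unequal variances, a t-test allowing for that; and "Wilcoxon rank-sum test will be used if data does not conform to a normal distribution". It closes with "The 95% confidence interval will be calculated, and" a P value below 0.05 "will be considered to indicate a significant difference".

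The general rule neither names nor exempts the primary outcome. No normality test, threshold or unit of testing (each arm, or both pooled) is given. The Primary outcome section defines the endpoint as change in NRS (0–10) from baseline to the end of the last treatment in week 6.

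**The concern.** The main-outcome rule needs an estimate of the difference and an interval on the NRS scale. To find out how to obtain them, an analyst has only the general paragraph, and there the method depends on what the trial data look like. If the data are called non-normal, that paragraph leads to medians, a rank-sum test of no difference and a 0.05 threshold. None of these can be set against 2 points. A rank-sum P value below 0.05 does not refute non-inferiority, and one above 0.05 does not support it.

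At stake is whether the deciding analysis is fixed before the data are seen. As written, two analysts could follow the section in good faith and report different primary results.

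**Working it through.** **1. The plan's own sample size.** Inputs from Sample size calculation: margin 2, α 0.025 (taken as one-sided), power 80%, SDs 26.63 and 15.07. The figure of 29 per group reproduces if the SDs are divided by 10, the larger is used in both arms and the true difference is zero (all three are assumptions):

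n = 2 × (1.960 + 0.842)² × 2.663² / 2² = 27.8, so 28 by the normal approximation, and 29 with the t distribution (power 0.8025).

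This is a calculation for a difference in means against a margin. It does not depend on the Wilcoxon sentence.

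**2. Why the two criteria answer different questions.** The half-width of a t interval is t × SD × √(2/n). A deficit for ILM is significant if it exceeds the half-width; non-inferiority is shown if it is smaller than 2 minus the half-width. The t-test stands in here for the rank-sum test so that the arithmetic is visible.

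| n per arm | SD | Half-width | Significant if deficit exceeds | Non-inferior if deficit is below |
|---|---|---|---|---|
| 29 | 2.663 | 2.003 × 2.663 × √(2/29) = 1.40 | 1.40 | 0.60 |
| 37 | 1.507 | 1.993 × 1.507 × √(2/37) = 0.70 | 0.70 | 1.30 |

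In the first row, an observed deficit between 0.60 and 1.40 is not significant, yet non-inferiority is not shown. In the second, a deficit between 0.70 and 1.30 is significant, yet non-inferiority is shown. The criteria diverge in both directions.

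**3. The same with the rank-sum test itself.** Simulated integer NRS data with entry at 4 or more and bounds of 0–10, difference coded as improvement (ILM minus TM). The bounds slightly shrink the nominal deficits.

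- n = 28, SD 2.66, deficit 1.5: the rank-sum test is non-significant in 48% of trials; the interval shows non-inferiority in 15%.
- n = 37, SD 1.5, deficit 1: the rank-sum test is significant in about 77%; the interval shows non-inferiority in 82%; both occur together in 60%.

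**4. How often the normality branch could be triggered.** Assumptions: rounded-normal change scores and Shapiro-Wilk at 0.05. Share of trials with a rejection (4,000 runs per cell):

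| n per arm | SD | Either arm | Arms pooled |
|---|---|---|---|
| 29 | 1.5 | 66.8% | 90.1% |
| 29 | 2.1 | 32.3% | 39.3% |
| 29 | 2.66 | 21.4% | 19.4% |
| 37 | 1.5 | 83.3% | 99.1% |
| 37 | 2.1 | 39.9% | 54.5% |
| 37 | 2.66 | 24.2% | 26.4% |

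With the entry criterion and the scale bounds added, and 28–37 per arm, the either-arm range is about 30–87% for change scores and 34–88% for week-6 scores. In the table the underlying variable is normal, so those rejections come from rounding and chance alone.

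**5. Rank methods that do carry a margin.** A rank-sum test shifted by 2 points tracks the interval rule: 0.85 against 0.88 (n = 28, SD 2.66, deficit 0) and 0.79 against 0.82 (n = 37, SD 1.5, deficit 1). The plan names neither this test nor a Hodges-Lehmann interval. The latter is coarse on whole-number scores: its limits tend to fall on whole numbers, so a lower limit strictly above −2 in effect means −1 or better. At n = 37, SD 2.1 and deficit 1 it met the criterion in 17% of trials, against 61% for the t interval.

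**The case against.** The strongest reply is that the main outcome has its own rule, without conditions, and that a specific rule governs over a general one. The general paragraph also has to serve WOMAC, SF-36, knee circumference, the walking test and the weekly NRS. Its closing sentence promises a 95% interval, and nowhere is P above 0.05 said to show non-inferiority. This stands. A reader might infer that the plan swaps its non-inferiority analysis for a rank-sum test; the text does not say so.

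A reader might also argue from the chance that a difference test misses a moderate true deficit, say half an SD. That does not show a wrong conclusion: at SDs of 1.5–2.7, half an SD is 0.75–1.35 points, inside the margin, so ILM would be non-inferior by the plan's own definition.

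It is also fair that no distribution, normality test or threshold is given, so the trigger rates rest on assumptions, and that an article may leave computational detail to an analysis plan. But the section is not silent on method. It states a data-dependent choice for continuous data, does not exempt the primary outcome, and in one branch names a test that cannot be set against the margin. That is a poorly fixed rule, not just an omitted detail.

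**Conclusion.** The point holds as a defect in how the primary analysis is fixed. The criterion is sound in form, but the method behind its interval is unstated, and the only stated methods are picked by checks on the trial data. The unshifted rank-sum branch cannot answer the non-inferiority question; a margin-shifted rank method could, but none is specified.

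The non-normal branch is a realistic prospect: roughly 20% to over 80% of trials, assuming SDs of 1.5–2.7, about 29–37 per arm and Shapiro-Wilk at 0.05 in either arm. Pooling the arms takes the upper end to almost certain. These are not rates of wrong conclusions. They show how often an analyst could reach a branch in which the section names no usable interval.

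**What to change.** State that the primary non-inferiority decision rests on the 95% confidence interval for the mean NRS difference (ILM against TM) at week 6, from an ANCOVA adjusted for baseline NRS, or else from an unequal-variance t interval. Choose one in advance and compare it with the 2-point margin whatever normality or variance checks show. Drop those checks for the primary outcome and limit the Wilcoxon rule to other comparisons. Optionally, report a Hodges-Lehmann shift with its 95% interval against the same margin, as a sensitivity analysis only, given its coarseness on whole-number scores.

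The cost is a few sentences, settled before the data are analysed, plus the Ethics Committee approval that Study quality control and data management requires for protocol changes. Baseline NRS is already collected. The sample size stays at 29 per group, since it was derived for a difference in means. Making a margin-shifted rank test primary would instead need about 28 × π/3 = 29.3, or 30 per group, under normality.

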#### Primary outcome

The primary outcome, to be assessed at the end of the last treatment at week 6, is the change in pain from baseline using the NRS index [38]. The NRS index typically uses a 0–10 range instead of words to represent the degree of pain experienced by the subject: 0 indicates no pain; 1–3 indicates mild pain (occasional pain that generally does not interfere with walking); 4–6 indicates moderate pain (frequent pain that interferes with walking); 7–9 indicates severe pain (sustained pain that seriously interferes with or prevents walking); and 10 indicates the worst/overwhelming pain. At the time of the evaluation, participants will be asked to mark the number on the scale that best represents their pain level in the last 24 h.

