#### Secondary outcomes

The NRS pain score will also be measured at the end of the last treatment each week (weeks 1, 2, 3, 4, and 5). Other secondary outcomes will include the changes in WOMAC, SF-36, knee circumference, and 6-min walking test (6MWT) from baseline to endpoints (weeks 6 and 10):WOMAC: This scale evaluates the comprehensive condition of the knee joint from three aspects: knee pain, stiffness, and daily functional activities. The WOMAC scale contains 24 items, with four points for each item. A higher score signifies worse knee function. The Chinese version of this scale has good reliability and validity [39].SF-36: This scale consists of 36 items, including eight fields of physical function, arole physical, physical pain, general health status, vitality, social function, arole emotional, and mental health, and is used to assess the health-related quality of life of the subject. A higher score indicates better health-related quality of life [40, 41].Knee circumference: The degree of swelling in the subject’s knee was assessed by measuring the knee circumference (i.e., the leg circumference at the center of the upper and lower edges of the patella) in millimeters. A uniform tape measure will be used to measure different patients [42].6MWT: Before the test, researchers will draw a 30-m straight line on flat ground and mark both ends of the line. During the test, the participants will walk back and forth in a straight line at their own speed. The researchers will give the correct time every two minutes and calculate the distance walked by the participant at the end of six minutes. Potential discomfort such as fatigue, dizziness, angina pectoris, dyspnea and cold sweat will be recorded during the trial. The trial will be suspended or discontinued if the patient cannot complete it. During the test, participants will be monitored with a unified wristwatch for basic indicators such as heart rate and blood oxygen. The Borg score of dyspnea and fatigue and other data will be recorded before and after the test (Table 2) [43].

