### Safety assessment

The safety assessment will primarily include the recording of adverse events (AEs) and serious AEs, laboratory analyses, and monitoring throughout the exercise test. AEs occurring during treatment and follow-up will be recorded by the investigator on AE questionnaires within 24 h of their occurrence. In addition to recording the time, severity, reaction, treatment, and prognosis of the AEs, the questionnaire will also focus on recording the potential relationship between AEs and TM or ILM treatment. The most common treatment-related AEs include skin redness, pruritus, scalding, blisters, and dizziness. If the AE is severe, the patient will be suspended or withdrawn from the study and receive corresponding medical care or compensation. In addition, blood routine and C-reactive protein (CRP) measurement will be conducted before and after treatment. Lastly, a uniform sports wristwatch will be used to monitor the participants’ heart rates during the 6-min walk test.

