### Sample size calculation

This study is a randomized controlled non-inferior trial. Based on the literature, the smallest clinically significant difference in the pain NRS is 2 points [44–46]. Thus, we set the non-inferiority margin to − 2. The NRS score of the subjects after treatment was taken as the main outcome index. According to the results of similar studies, [47] the average NRS score of the experimental group was 40.53 ± 26.63, and that of the control group was 41.58 ± 15.07. So we used PASS 15 to calculate the sample size (29 participants in each group), *α* = 0.025, 1 − *β* = 80%. Considering that a maximum of 25% dropped out during the trial, we ultimately plan to recruit 74 participants (37 in each group) to ensure the target sample size is obtained. The calculation results of sample size are provided as Additional file 2.

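### LOCF for the week-6 NRS makes the error rate of the non-inferiority test depend on when, and in which arm, patients drop out

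*Protocol article*

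**What the plan says.** The main endpoint is described in these words: "to be assessed at the end of the last treatment at week 6, is the change in pain from baseline using the NRS index". It is judged by whether the lower limit of a 95% confidence interval lies above the margin: "The margin of non-inferiority is -2" (Primary outcome; Statistical analysis). The only provision for incomplete data is "Missing data will be replaced according to the last observation carried forward method", with no restriction by outcome or analysis set.

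Three other statements bear on it:

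- The ITT set is everyone randomised who had at least one treatment. A per-protocol (PP) analysis is run beside it and needs compliance of 80% or more and no prohibited treatment (Statistical analysis).
- The sample size allows for the possibility that "a maximum of 25% dropped out during the trial" (Sample size calculation).
- The NRS "will also be measured at the end of the last treatment each week (weeks 1, 2, 3, 4, and 5"), so a patient who leaves after week 1 has post-baseline scores on record (Secondary outcomes).

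**The concern.** LOCF enters a baseline or early-week score as if it had been observed at week 6. Change from baseline is zero in both arms at the start, so a carried-forward baseline score contributes no between-arm difference. This can happen here: one session is enough to enter the ITT set, and the first post-baseline NRS comes only at the end of week 1.

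If the difference between arms builds up gradually and both arms lose similar numbers, the week-6 difference is diluted. In a non-inferiority test, dilution helps the new treatment pass. At the planning maximum about 9 of 37 values per arm (0.25 × 37 = 9.25) would be carried forward, which is enough to change the error rate of the main test.

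**Working it through.** **Inputs from the protocol article.** Margin -2; two-sided 95% interval, so 2.5% on the relevant side; 29 evaluable and 37 recruited per arm; up to 25% dropout; planning SDs 26.63 and 15.07, which become 2.66 and 1.51 on the 0–10 scale.

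**The plan's own figure.** With SD 2.663 in both arms and a true difference of 0, the normal formula gives n = 2 × 2.663² × (1.960 + 0.842)² / 2² = 27.8, so 28. The noncentral-t version gives 29, the stated number. SD 2.66 is therefore the value implied by the plan and is used below. The stated 37 per arm follows from 29 × 1.25 = 36.25.

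**Assumptions not in the documents.** Within-patient correlation 0.5–0.6; dropout unrelated to outcome; last visit spread evenly over weeks 0–5 or weeks 1–5; the time course of the difference. In the unequal-dropout cases, TM patients improve by 3 points linearly over six weeks. Differences are in improvement, ILM minus TM, so a deficit is negative. The true week-6 difference is set at the margin, -2.

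**Expected LOCF estimate, equal dropout d.** It is -2 × [(1 - d) + d × m], where m is the mean share of the week-6 difference present at a dropout's last visit.

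- Linear, weeks 0–5: m = (0+1+2+3+4+5)/6/6 = 0.417; -2 × (0.75 + 0.104) = -1.71.
- Linear, weeks 1–5: m = 0.5; -2 × 0.875 = -1.75.
- Plateau from week 2, weeks 0–5: m = 4.5/6 = 0.75; -1.875. Weeks 1–5: m = 4.5/5 = 0.9; -1.95.
- Late build (squared share), weeks 1–5: m = 55/36/5 = 0.306; -1.65.
- Mid-trial peak (shares 0.5, 1, 1.4, 1.3, 1.15): m = 1.07; -2.035.

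**Unequal dropout, weeks 1–5.** The arms are computed separately.

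- Linear, ILM 10% / TM 40%: 1 × 0.95 - 3 × 0.80 = -1.45.
- Linear, ILM 40% / TM 10%: 1 × 0.80 - 3 × 0.95 = -2.05.
- Plateau, ILM 40% / TM 10%: mean ILM improvement at the last visit is (-0.5 - 1 - 0.5 + 0 + 0.5)/5 = -0.3; (0.6 × 1 + 0.4 × -0.3) - 2.85 = 0.48 - 2.85 = -2.37.

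**False non-inferiority by simulation.** 37 per arm, 95% interval against -2, at least 5,000 trials per setting. The Monte Carlo standard error at 5.3% and 5,000 trials is √(0.053 × 0.947/5000) = 0.3 points. Ranges cover separate runs with differing correlations and seeds.

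| Dropout ILM/TM | Time course | Last visit | Expected estimate | False non-inferiority |
|---|---|---|---|---|
| 25/25 | linear | 0–5 | -1.71 | 6.4–7.7% |
| 25/25 | linear | 1–5 | -1.75 | 5.3–6.8% |
| 25/25 | late | 1–5 | -1.65 | 7.7% |
| 25/25 | plateau | 0–5 | -1.875 | 3.6–4.1% |
| 25/25 | plateau | 1–5 | -1.95 | 2.8–3.1% |
| 25/25 | mid-trial peak | 1–5 | -2.035 | 2.0% |
| 10/10 | linear | 1–5 | -1.90 | 3.4% |
| 10/40 | linear | 1–5 | -1.45 | 13.3% |
| 40/10 | linear | 1–5 | -2.05 | 2.0% |
| 40/10 | plateau | 1–5 | -2.37 | 0.4% |

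At 10% dropout with last visits over weeks 0–5 the linear case gave 3.4–4.2%. With SD 1.5 in both arms, the 25% linear case (weeks 1–5) rose to 9.2%. A separate run of the 40/10 plateau case gave 1.2–1.7%, still below nominal.

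A likelihood repeated-measures analysis of the weekly scores, with covariance taken as known, stayed at 2.3–2.7% in all the weeks 1–5 settings. Completers alone gave 2.0–2.6%, as expected when dropout is unrelated to outcome.

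**PP set.** Three sessions a week for six weeks is 18. If compliance means sessions attended, 80% is 14.4, so at least 15 sessions, or five full weeks. Keeping only patients with a score at week 5 or later in the linear 25% case gave about 2.4–2.9%.

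**The case against.** A reader might infer that LOCF necessarily shrinks the difference and inflates false non-inferiority. The documents do not support that. They give no time course for the difference and no dropout by arm or by week. An early plateau leaves little inflation, and a mid-trial peak or heavier loss from ILM can make LOCF conservative. The 25% is also a planning ceiling: "Considering that a maximum of 25% dropped out during the trial". These points stand, so the direction has to be stated as conditional.

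The PP analysis is a second fair point. It excludes most early leavers, and in the linear 25% case requiring ITT and PP both to succeed gave 2.2–2.4%. The Statistical analysis section does not require both, however. PP also selects on behaviour after randomisation, and its near-nominal rate relies on dropout unrelated to outcome. Nor should ITT be called the primary analysis here: that section attaches the word primary only to its PP sentence.

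Third, with a severe adverse event "the patient will be suspended or withdrawn from the study" (Safety assessment), and LOCF then freezes whatever relief had been reported. It is tempting to count this as a further harm that a mixed model would cure. The effect was not quantified, and a mixed model assumes missing at random, so it does not remove the problem.

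**Conclusion.** The point holds in conditional form. LOCF is the only method fixed for the week-6 ITT test, and its bias depends on the timing and balance of dropout, neither of which can be known in advance. Under similar dropout and gradual divergence it is anti-conservative: at SD about 2.66, correlation 0.5–0.6 and a true deficit of 2, the rate is roughly two to three times the nominal 2.5% at 25% dropout. The excess is about 1 to 1.5 points at 10% dropout or with an early plateau. Across unequal dropout and a mid-trial peak, the rate ran from well below nominal to about five times it (13.3/2.5). The correlation, dropout pattern and time course are assumptions, not facts from the protocol article. The change should be made, because the main test should not depend on the dropout pattern in this way when the data to avoid it are already collected.

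**What to change.** For the primary NRS outcome, replace LOCF with a likelihood-based mixed model for repeated measures on weeks 1 to 6, with arm, week, arm-by-week interaction and baseline NRS. Compare the 95% confidence interval of the week-6 contrast with the margin. Because this model assumes missing at random, a sensitivity analysis for dropout not at random is an optional addition.

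The cost is small: no new visits or measurements, slightly more analysis work, and possibly a somewhat different interval width. Patients who leave before the first weekly score contribute no outcome to this model, so their number by arm should be reported. The change needs Ethics Committee approval, as the section on study quality control and data management requires for any protocol change.

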## Discussion

In recent years, as the state attaches great importance to the scientific research and innovation of the TCM industry, the combination of TCM instruments and modern science and technology has become increasingly close, which has become a new direction for the development of TCM instruments. However, the transformation of TCM needles and instruments mostly stays in the original appearance, rarely using new technology, new materials and upgrading its core technology. Modern technologies such as infrared, laser and acupoint stimulation have been widely used in the research and development of TCM instruments, but many of them have a single stimulation mode, which is easy to cause body tolerance and cannot achieve the effect of TM therapy. For the imitation moxibustion instruments on the market, the accurate simulation of TM cannot be achieved [48]. Some of them are different from traditional moxibustion in terms of shape, size and heating area [49], some simply simulate the thermal effect of moxibustion sticks, lack of discussion and application of other functional factors [21–23]. At the same time, due to the differences in moxibustion materials, amount, application methods, burning conditions and the performance of infrared spectroscopy instruments for measurement over the past years, it is difficult to form a unified standard for the characteristics of moxibustion infrared spectrum, let alone realize accurate simulation of it [24]. Therefore, making full use of modern sensing technology, artificial intelligence, biophysics and other new technologies, infrared ceramics/graphene and other new materials, breaking through technical bottlenecks, and establishing a common key technology platform based on the principles of TCM diagnosis and treatment are the key breakthroughs in the current research and development of TCM medical devices.

Based on the above reasons, we have realized the full band infrared emissivity test of moxibustion in the early stage and developed ILM which can realize accurate simulation of the temperature and emission spectrum of moxibustion combustion (the internal temperature is 736 °C; the external working temperature is about 470 °C; the wavelength corresponding to the peak of the emission spectrum is 3.98 μm) and effectively makes up for the defects of TM and existing moxibustion instruments [25, 37].

This study will be the first clinical trial to evaluate infrared ceramic/graphene laser moxibustion for the treatment of KOA. The study will test the hypothesis that ILM is not inferior to TM for the treatment of KOA. The Zelen-design adopted in this study is consistent with the real diagnosis and treatment environment, thereby minimizing the bias inherent in the traditional design of randomized controlled trials. During the trial, the willingness of patients or their guardians receive different treatments will be considered to help ensure the compliance of patients and the smooth conduct of the trial.

The primary priority in the treatment of KOA is pain relief followed by maintaining normal knee function and improving quality of life; thus, we chose pain on the NRS as the primary outcome and WOMAC, SF-36, knee circumference, and 6MWT as the secondary outcomes. For the safety evaluation, in addition to recording AEs, we will also conduct blood routine and CRP detection before and after the trial. CRP is one of the most commonly used laboratory indicators of systemic inflammatory diseases. The expression of CRP increases in patients with OA and is closely related to the progression and prognosis of the disease [50, 51].

The proposed study has some limitations that should be acknowledged. First, this is a non-inferiority trail; thus, compared with superiority trials, some participants may have greater difficulty adhering to the protocol for their treatment. This may result in incorrectly rejecting the null hypothesis [50]. For this reason, the Zelen-design was used to improve patient compliance. Second, it is difficult to blind the researchers involved in the assignment and treatment due to the differences in the nature of the treatments. Therefore, to reduce the risk of bias, the study evaluation will be conducted by people not involved in assignment or treatment. Third, this will be a small-scale trial with a small sample size. Finally, this study will primarily use subjective scales to evaluate knee joint pain and function; objective physiological indicators are lacking.

The results of our study will help preliminarily determine whether the infrared ceramic graphene moxibustion device is non-inferior to traditional moxibustion in alleviating knee pain and improving related function in KOA patients, therefore providing a suitable alternative for TM in clinical practice. In the future, based on the results of this exploratory study, we hope to design and carry out a multicenter, large-sample, randomized controlled clinical trial with a longer follow-up period to confirm the results and enhance the generalizability of the findings.

